**Methods/design:**

Elderly (≥70 years of age) patients admitted to the Royal Melbourne Hospital with delirium, and not requiring surgery, will be identified from the current practice of the investigators and through referral by other general medical unit staff. To facilitate this, other staff will be briefed on the project by investigators. Patients will be recruited with suitable informed and documented consent (person responsible) by the study investigators. They will receive orally either 5 mg melatonin (18 patients) or placebo (18 patients) nightly for 5 nights (or until discharged).

During treatment, participants will be assessed by study staff using a validated scale of delirium severity (the Memorial Delirium Assessment Scale), and a validated measure of delirium state (Confusion Assessment Method) to determine if melatonin decreases the severity or the duration of delirium. Assessment will continue for a further two days after treatment has ceased, to determine if the treatment causes persisting abatement of symptoms, and to assess for adverse events.

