## Background

Delirium is a clinical syndrome of acute onset characterised by fluctuating attention and awareness with a disturbance in cognition due to the direct physiological consequence of a medical condition, intoxication, withdrawal, toxin, or multiple aetiologies [1]. Melatonin (N-acetyl-5-methoxytryptamine) is a hormone (and likely neurotransmitter) produced by the pineal gland in the human brain. It is involved in sleep/wake cycle regulation. Delirium is a condition with little research into the underlying mechanism, but felt to be most commonly related to abnormalities of brain neurotransmitters.

**Table 1 Tab1:** Schedule of Procedures

Procedure	Entry (D0)	Daily 1–5 (on treatment)	Day 6	Final Visit (Day 7)
Consent	○			
Age	○			
Gender	○			
Electrolytes	○			
Liver function	○			
MMSE	○	○	○	○
Digit Span	○	○	○	○
CAM	○	○	○	○
MDAS	○	○	○	○
Motor type	○			
CMI	○			
IQCODE	○^a^			
GDS-15	○			
Katz ADL	○			
Presence of Restraints		○	○	○
# Falls		○	○	○
# Pressure areas	^b^	○	○	○
Rescue medication		○	○	○
Adverse events			○	○
Review INR	○^c^	○^c^		

^a^Ideally the IQCODE will be measured at entry but can be measured at any point

^b^Initial number and location will be recorded at entry in order to derive the number of new areas at each subsequent visit

^c^If participant is on warfarin, we will review the INR that has been performed every 1–2 days as is standard protocol for acutely unwell inpatients when warfarinised

Delirium is a common clinical phenotype with a variety of potential precipitating factors on the background of predisposing factors. The clinical phenotype does not appear to vary with cause [2], and therefore research into the treatment of delirium can be conducted without reference to aetiology. An exception is Delirium Tremens, a specific syndrome caused by withdrawal from chronic alcohol consumption. This is regarded separately from delirium and is not the topic of the proposed study.

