### End points

#### Primary

Change in MDAS score from baseline to average over days 1–5

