### Study population and recruitment

During multidisciplinary meetings and the day-to-day duties of investigators, potential patients will be considered for inclusion. Patients with a diagnosis of delirium via the CAM and who are 70 years or older as general medical inpatients will be screened according to exclusion criteria. These exclusion criteria include solely hypoactive delirium (MDAS question 9), planned surgery, the inability to speak or understand English, severe sensory impairment or dysphasia, an expected prognosis or discharge of less than 7 days, severe hepatic failure (defined as Bilirubin ≥2.5 times upper limit of normal; alkaline phosphatase, aspartate transaminase and/or alanine transaminase > 3 times upper limit of normal), a markedly non-therapeutic INR (<1 or >4), use of melatonin or melatonin receptor agonist in the preceding 14 days, active seizure disorder (a seizure in the last month, or a seizure disorder not on anticonvulsants), and concomitant cimetidine use. As melatonin is a sedative medication, it’s clinically inappropriate to provide this to patients who have an exclusively hypoactive delirium as this may exacerbate the decreased conscious state. Also, as per Balan et al. [3], an exclusively hypoactive delirium may be associated with an elevated melatonin level. Patients who have surgery planned during the study period are to be excluded as surgery and anaesthesia are independent risk factors for delirium and would act as intra-intervention confounders.

Given patients with delirium are unable to provide informed consent, consent will be obtained by the person responsible for surrogate decision making and documented on clear consent forms. The surrogate decision maker retains the capacity to withdraw the patient from the trial at any time. If during the course of the trial the patient regains capacity due to the resolution of their delirium, a separate informed consent will be obtained should the patient wish to continue; if they do not, they will be withdrawn from the trial.

The Melbourne Health Human Research and Ethics Committee has evaluated and approved this trial.

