### Power analysis

The primary endpoint is a decrease in MDAS score from the baseline to the average score across days 1–5 of treatment. As a pilot trial, one of the feasibility objectives is to obtain the standard deviation for the primary outcome measure in order to allow a power calculation to be performed to assist with the development of an appropriately powered trial to test the relevant hypotheses. As such, no true power calculation can be calculated.

However, a trial of the prophylactic use of melatonin in a Canadian hospital [7] yielded entry data of an MDAS score of 11.4 with a standard deviation (SD) of 3.0. A clinically significant change on the MDAS (highest possible score of 30, lowest of 0, positively correlated with severity) of 3 points at 80 % power and a significance level of 5 % suggests 16 patients per arm. At a 10 % dropout rate and rounding up, the groups should be of 18 patients each.

It should be noted that these figures cannot be used to precisely calculate power, as they use MDAS score at entry into the trial (not during treatment), and the population is significantly different with an average length of stay of 14 days (around twice that of similar patients at RMH). While these results provide some guidance that a trial is possible and relevant group size and power achievable, a pilot is still required to confirm the exact numbers needed.

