### Statistics

Data will be collected for each patient on a daily basis, up to 7 days following recruitment. The primary and secondary outcome measures will be compared using standard statistical methodology. For continuous variables, results will be compared using a Students’ t-test with significance set to 0.05 if they are normally distributed, else a Mann-Whitney or other non-parametric test will be utilised. Control and treatment group homogeneity will be tested with Chi-square statistics. For discrete outcomes, results will be tested using a Chi-square test. Risk ratios will be employed where appropriate. The Hausman specification test will be used to determine whether the data should be analysed using either fixed or random effects, though it is expected that a random and fixed (mixed) effects model will be required.

Extensions to the statistical methods above may be required depending on what is found once the data is collected and the analysis is begun.

Missing data will be accounted for using the last observation carried forward method, and all data will be analysed according to the intention-to-treat principle primarily (and per-protocol analysis secondarily).

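### Last observation carried forward as the only missing-data rule fills days 6–7 with on-treatment scores, and biases the days 1–5 comparison if exit or recovery differs by arm

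*Protocol article*

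**What the plan says.** The protocol article fixes the handling of missing data in one sentence of its Statistics section: "Missing data will be accounted for using the last observation carried forward method". The same sentence continues that "all data will be analysed according to the intention-to-treat principle primarily (and per-protocol analysis secondarily". The rule is not restricted by endpoint, day or reason for missingness. A little earlier, the section says that a model with fixed and random effects will probably be needed.

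The primary endpoint is "Change in MDAS score from baseline to average over days 1–5". The first secondary endpoint is the change from the days 1–5 average to the days 6–7 average. The abstract gives its purpose: "Assessment will continue for a further two days after treatment has ceased, to determine if the treatment causes persisting abatement of symptoms".

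Four other statements bear on who will have missing days:

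- Treatment is given "nightly for 5 nights (or until discharged" (abstract, Methods/design).
- When a patient regains capacity, "a separate informed consent will be obtained should the patient wish to continue; if they do not, they will be withdrawn from the trial" (Study population and recruitment).
- The earlier trial used for planning had an "average length of stay of 14 days (around twice that of similar patients at RMH" (Power analysis).
- Patients expected to be discharged in under 7 days are excluded at entry (Study population and recruitment).

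**The concern.** Carrying the last score forward assumes that the patient would have stayed at that score. The Background defines delirium by "fluctuating attention and awareness with a disturbance in cognition", and the trial is built around its abatement, so a frozen score is a poor guess at the days that follow.

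The missing days are also unlikely to be a random subset. Discharge and withdrawal on regaining capacity both tend to follow recovery. If melatonin speeds recovery, it may change who has missing days and when.

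The endpoint most exposed is the post-treatment one. The Background says that abatement after an effective treatment stops would be evidence of cure, and days 6–7 are the only off-treatment observations. For a participant last seen on or before day 5, the rule supplies those two days from a score taken during treatment.

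**Working it through.** **The plan's own figure.** The Power analysis uses a 3-point difference, SD 3.0, 80% power and 5% significance. Two-sided, n = 2 × (1.960 + 0.842)² × 3.0² / 3² = 15.7, so 16 per arm. Then 16 / 0.9 = 17.8, so 18 per arm. Both stated figures reproduce, and nothing below alters them.

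**One patient.** Assume a steady improvement of 1 point per day; the documents give no recovery rate. The true primary change is -(1+2+3+4+5)/5 = -3.0. The true days 6–7 change is -6.5 - (-3.0) = -3.5. With the last score carried forward:

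| Last visit | Primary change | Shortfall | Days 6–7 change | Shortfall |
|---|---|---|---|---|
| Day 1 | -1.0 | 2.0 | 0.0 | 3.5 |
| Day 2 | -1.8 | 1.2 | -0.2 | 3.3 |
| Day 3 | -2.4 | 0.6 | -0.6 | 2.9 |
| Day 4 | -2.8 | 0.2 | -1.2 | 2.3 |
| Day 5 | -3.0 | 0 | -2.0 | 1.5 |
| Day 6 | -3.0 | 0 | -3.0 | 0.5 |

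For a last visit on day 5 or earlier, the days 6–7 figure is made entirely of on-treatment scores. This holds whatever the recovery rate.

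**Arm means with no drug effect.** Assume that both arms improve by s = 0.9 points per day and that exit is random at rate h per day after each visit from day 1 to day 6. The chance that day k is the last visit is h(1-h)^(k-1). The mean shortfall in an arm is s × Σ (shortfall at k) × h(1-h)^(k-1), using the table's columns.

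| Daily exit h | Primary shortfall | Days 6–7 shortfall |
|---|---|---|
| 5% | 0.9 × 0.193 = 0.17 | 0.9 × 0.642 = 0.58 |
| 10% | 0.9 × 0.371 = 0.33 | 0.9 × 1.178 = 1.06 |
| 20% | 0.9 × 0.689 = 0.62 | 0.9 × 1.990 = 1.79 |

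The bias in the comparison is the difference between the arms' shortfalls:

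- Equal exit: zero for both endpoints.
- 5% versus 10%: 0.33 - 0.17 = 0.16 points (primary); 1.06 - 0.58 = 0.48 (days 6–7).
- 5% versus 20%: 0.62 - 0.17 = 0.45 points (primary); 1.79 - 0.58 = 1.21 (days 6–7).

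Simulation with 18 per arm, between-patient SD 2.2 and within-patient SD 2.0 agrees: primary bias 0.16 and 0.46. The type I error of the primary t-test was 5.2% to 5.7% at 5% versus 10%, and 8.3% at 5% versus 20%.

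**A working drug.** Assume improvement of 0.5 (placebo) and 1.5 (active) points per day, with exit at 20% to 40% per day once MDAS is below 7. Differences are active minus placebo.

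- The primary difference shrinks from -2.87 to between -2.67 and -2.51.
- The days 6–7 difference shrinks from -2.48 to between -1.79 and -1.34.
- If active patients instead worsen by 1 point per day after treatment stops, a true days 6–7 difference of +0.25 becomes -0.06 to -0.21. The rebound is hidden.
- Equal random exit of 10% per day is not harmless when recovery differs: the primary difference goes from -2.87 to -2.54 and the days 6–7 difference from -2.48 to -1.71.

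**The case against.** The strongest reply is that this is a pilot, that the primary bias is modest and conditional, and that selection limits early exit. Much of that stands. Several stronger readings should be set aside.

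- **That the primary comparison is biased whatever happens.** With no effect and equal exit the bias is zero. A type I error of 8.3% needs melatonin to change exit fourfold without changing MDAS, which nothing in the documents suggests. At a twofold difference it is close to nominal. With a working drug, the primary effect is merely diluted.
- **That 30% to 50% will leave early, which refutes the 10% dropout allowance.** Exponential remaining stays with means of 14 and 10 days would give 30% and 39% gone by day 5, and 39% and 50% by day 7. But the distribution and means are assumptions. A constant hazard places exits early, where the exclusion of expected discharge within 7 days acts. The stay of about 7 days describes similar patients at the hospital, not this selected cohort. The article also does not say that assessment stops at discharge; that is inferred from daily inpatient visits.
- **That falls, restraints and rescue drugs would be repeated on unobserved days.** The sentence is unrestricted, but the article describes no such operation and defines these endpoints as counts or doses over days 1–5.
- **That the SD the pilot is meant to supply is spoiled.** In simulation it moved from 2.63 to between 2.72 and 2.78, or 3% to 6%. Sampling error of an SD from 36 patients is about 1/√(2 × 35) = 12%.
- **That dropping the rule brings a large gain in precision.** A simulated comparison gave an SD of the estimate of 0.64 for a baseline-adjusted mixed model against 0.81 for an unadjusted t-test. With no missing data at all, baseline adjustment alone took it from 0.73 to 0.60, so most of the gain has another source.

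None of this rescues the rule for days 6–7. The exclusion rests on a forecast at entry, the abstract still provides for discharge during treatment, and withdrawal on regaining capacity is untouched by it.

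**Conclusion.** The point holds in two parts of unequal strength.

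For days 6–7 it holds by construction. Any participant last seen on or before day 5 contributes no off-treatment information, yet is counted as if there were some. Under the no-effect assumptions, unequal exit produces a bias of about 0.5 to 1.2 points. The direction is not fixed: the rule can dilute a real benefit, hide a rebound, or create a difference where there is none.

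For days 1–5 it is conditional. Bias needs exit or recovery to differ by arm, and is about 0.16 to 0.45 points in the no-effect cases, against the 3-point change that the Power analysis treats as clinically significant.

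The sizes rest on assumed recovery and exit rates, since the documents give neither. In a pilot, with the main damage to a secondary endpoint, this is a should-fix.

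**What to change.** Replace the carry-forward sentence with the mixed model that the Statistics section already expects. Fit it by likelihood to the observed daily MDAS scores, with treatment, day, treatment-by-day, baseline MDAS and a random patient effect. Read off the average days 1–5 contrast and the days 6–7 contrast from that model, without imputation. Record the reason for each missing day. Add one sensitivity analysis for participants who leave after recovery. Carrying forward may stay only as a sensitivity analysis for days 1–5, and should not be used for days 6–7.

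The cost is one rewritten sentence and one more item on the daily record, with no extra patients or visits. The small downside is reliance on data being missing at random given the observed scores, which the sensitivity analysis is there to probe. The model cannot create off-treatment observations for those who left early, so the number actually seen on days 6–7 should be reported by arm.

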## Discussion

A large quantity of both scientific and journalistic literature has been generated about the increased number of older persons living worldwide. The risk of developing delirium increases as one ages. Given that delirium has significant health costs to patients, as well as being a significant financial burden to families and to society, an effective treatment for delirium would mitigate against these costs – and no such treatment currently exists. A pilot RCT was selected to appropriately assess the relevant outcome measures as discussed above, and to generate data for powering a larger study in the future. Acute general medical inpatients as a population are at significant risk for developing delirium, and are among a group that we expect to see significant benefit in and for should delirium treatment/cessation be successful. This, in conjunction with not excluding patients with dementia, should allow for greater external validity of the results, and also informs the practice for a large proportion of hospital inpatients.

Our work should allow for further information as to whether melatonin is able to provide therapeutic as well as prophylactic benefit, and as a pilot also guide the powering of further larger trials if they are warranted in the future.
